#### Correlation analysis between clinical and imaging data

The MATLAB software will be used to conduct the correlation analysis between ReHo values and clinical indexes of PSD. Gender, age, and course will be included as covariates in a Pearson correlation study between the MMT score, Fugl-Meyer score, and ReHo values of PSD. The statistical threshold of *P* < 0.05 will be considered statistically significant.

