We intend to perform fMRI scanning and TMS-MEP technique to observe the OAKT in cerebral function, motor neural function, and dyskinesia improvement to determine the potential mechanism of OAKT in the rehabilitation of PSD. Through correlation analysis of functional neuroimaging, neurotic electrophysiological, and clinical data, it will be contributed to investigating the central-peripheral coupling effect of OAKT on PSD and to further clarify the neurological processing of acupuncture kinesitherapy covering the entire pathway from peripheral to central nervous system.

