### Outcomes

#### Clinical outcomes

MMT Freehand Muscle Strength Grading and Simplify Fugl-Meyer grading will be evaluated at baseline and study completion. With 11 grades, MMT is used for measuring muscle contraction force based on muscle ability to accomplish gravity-support, anti-gravity, or anti-resistance tasks. Muscle strength increases with grade level. Fugl-Meyer is a motor function evaluation scale that consists of 33 upper-limb and 17 lower-limb subscales. Each subscale is worth 0 to 2 points, for a total score of 100. The motor function improves with a higher score.

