#### Neurotic electrophysiology outcomes

Transcranial magnetic stimulation of motor evoked potential (TMS-MEP) examination will be used for neurotic electrophysiology. Cortical magnetic stimulation will be performed using the Keypoint evoked potential instrument and the magnetic stimulator MagII PR030 with standard circular coil and single puls form. The subjects assume a calm supine or seated position. The compound action potentials of the hand muscle (abductor pollicis brevis) will be recorded using a magnetic stimulator center at 175 px on both sides in the C3 and C4 areas, as well as a spinal cord stimulation center in the C7 area. Simultaneously, the compound action potential of the lower extremity muscle (tibialis anterior) will be recorded, with the coil center situated between 2 and 150 px in front of the CZ region. The intensity of the stimulus should gradually increase from low to 65–75% of the maximum output intensity on the scalp and 65–80% of the maximum output intensity on the lower limbs. Varying limbs can be stimulated at different positions and angles depending on the subject's condition. In order to establish the strong repeatability of compound muscle action potential (CMAP) waves, the complete inspection should measure 4–5 CMAP waves. The highest amplitude, shortest latency, and clearest waveform should be recorded.

The cortical region's amplitude (AMP), potential latency (PL), and central motor conduction time (CMCT) serve as the main markers of TMS-MEP. The outcomes can be categorized into 4 levels: (1) no MEP wave with strong repeatability and a clear and stable waveform is evoked during cortical stimulation; (2) prolonged PL in cortical stimulation; (3) prolongation of CMCT; (4) AMP in the affected side drops by more than half when compared to the healthy side. The last three are categorized as prolonged in this study and will be treated as aberrant MEP.

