Two advances in this study are the idea and the methodology. For the idea, we propose to conduct a prospective functional neuroimaging and neurotic electrophysiological study based on a case-control study in the PSD and HC groups as well as a self-control study in the PSD group. The primary motor cortex (higher center), the thalamus (higher center), the spinal cord (secondary center), and the muscle (peripheral) motor neural signal transmission channel are the targets of our assessment of PSD's abnormal central-peripheral neural function and the coupling effects of OAKT on PSD. For the technique, we propose doing a curative effect evaluation and mechanism investigation based on fMRI scanning, TMS-MEP examination, and the MMT and Fugl-Mayer scale assessment to examine the effects of OAKT on brain function, motor nerve function, and degree of motor dysfunction in PSD. Pearson analysis will also be performed between the MMT score, Fugl-Meyer score, and ReHo values of PSD to investigate the association of imaging, neurotic electrophysiological, and clinical outcomes, and to finally exploit the central-peripheral linkage control mechanism and coupling effect of OAKT on PSD from functional imaging and neurotic electrophysiology perspectives.

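### The correlation analysis meant to show central-peripheral coupling includes no TMS-MEP measure, although the Introduction and Discussion say it will link electrophysiology with imaging and clinical outcomes

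*Protocol article*

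**What the plan says.** The last paragraph of the Introduction gives the route to the coupling effect: "Through correlation analysis of functional neuroimaging, neurotic electrophysiological, and clinical data". That is three data domains.

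Under Statistical methods, the section on correlation between clinical and imaging data says that MATLAB will be used to "conduct the correlation analysis between ReHo values and clinical indexes of PSD". It then fixes the variables and covariates: "Gender, age, and course will be included as covariates in a Pearson correlation study between the MMT score, Fugl-Meyer score, and ReHo values of PSD". Its criterion is: "The statistical threshold of *P* < 0.05 will be considered statistically significant".

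The Discussion repeats the variable list, "Pearson analysis will also be performed between the MMT score, Fugl-Meyer score, and ReHo values of PSD", and in the same sentence gives its purpose: "to investigate the association of imaging, neurotic electrophysiological, and clinical outcomes".

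The Abstract and Study setting also describe the Pearson analysis as relating clinical to imaging outcomes. The electrophysiology section says that "amplitude (AMP), potential latency (PL), and central motor conduction time (CMCT) serve as the main markers of TMS-MEP". These markers are analysed under Clinical and electrophysiological data analysis, by tests that compare groups. On the clinical side: "With 11 grades, MMT is used for measuring muscle contraction force".

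**The concern.** The study is built around a pathway from motor cortex through thalamus and spinal cord to muscle. The fMRI covers brain, cerebellum and brain stem. The Introduction gives TMS-MEP the task of assessing motor neural conduction. A correlation between ReHo and a clinical score goes from one end of the pathway to the other without using the measure of what lies between.

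The stated correlation is also the only analysis in the article that joins data domains. ReHo otherwise gets paired t-tests, and the clinical and MEP data get group comparisons. If the plan is followed as written, the report could state that conduction changed and that ReHo changed, but would have no planned result on whether the two go together. A conclusion about coupling along the whole pathway would then rest on findings set side by side.

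**Working it through.** **1. Promise against plan.** The article states no power, effect size or sample size for the correlation analysis, so there is no figure to reproduce. The core check is textual.

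| Place in the article | Domains or variables |
|---|---|
| Introduction, last paragraph | imaging, electrophysiology, clinical |
| Discussion, stated purpose | imaging, electrophysiology, clinical |
| Discussion, listed variables | MMT, Fugl-Meyer, ReHo |
| Statistical methods, correlation section | MMT, Fugl-Meyer, ReHo |
| Abstract and Study setting | clinical, imaging |

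Correlations that involve amplitude, latency or conduction time: 0.

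The term for clinical indexes cannot be stretched to include MEP. Clinical outcomes are listed as MMT and Fugl-Meyer, electrophysiology has its own outcome section, and the analysis section for group comparisons names the two separately.

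**2. Multiplicity.** The criterion is 0.05 per test with no adjustment stated. The family-wise correction in the article belongs to the voxel-wise t-tests. The number of ReHo regions is not given, so it is assumed here. For m independent tests, P(at least one false positive) = 1 − 0.95^m. With two clinical scores:

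- 1 region, m = 2: 1 − 0.9025 = 9.8%
- 3 regions, m = 6: 26.5%
- 5 regions, m = 10: 40.1%
- 10 regions, m = 20: 64.2%

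The two scores both measure motor function in the same patients, so the tests are not independent, and these values illustrate the size only.

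**3. Arm as a covariate.** This matters only if post-treatment or change values are pooled over the three PSD arms. A simulation (20,000 runs, 3 × 15 patients, zero correlation within arms, one arm shifted in both variables by an assumed d SD, no other covariates) gave these rejection rates for the pooled Pearson test: 6.3% at d = 0.5, 13.0% at d = 0.8, 22.7% at d = 1.0 and 65.6% at d = 1.5. With arm terms the rate was about 5% throughout.

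**4. Cost of arm terms.** Inputs: n = 3 × 15 = 45 from Sample size; k covariates; two-sided 0.05; 80% power. Detectable partial r = tanh[(1.960 + 0.842)/√(n − k − 3)].

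- k = 3 (gender, age, course): tanh(2.802/√39) = 0.421
- k = 5 (plus two arm terms): tanh(2.802/√37) = 0.431

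n = 45 is the best case, because only subjects with complete data are analysed and the sample size allows for drop-out. At an assumed n of 36 the two values are 0.471 and 0.485.

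**The case against.** The strongest defence is that an article condenses a fuller plan, in which the MEP correlations may appear. That would answer a silence, but the article is not silent. It gives the variable list twice and attaches to it a purpose that the list cannot serve.

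The defence does succeed against several stronger readings that a reader might draw:

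- *The plan cannot address coupling at all.* The Discussion counts muscle as the peripheral end of the pathway, and MMT measures muscle force. ReHo with MMT is thus a partial central-to-muscle association in the protocol's own terms. Central and conduction effects are also each tested separately. What is absent is the link through MEP.
- *The plan correlates raw scores and pools the arms.* The correlation section does not say whether baseline, post-treatment or change values are used, or whether the arms are combined. Baseline correlations would need no arm term. Such detail may properly sit in a fuller document.
- *Significant correlations would mostly be false.* The 64% needs ten regions and independent tests, both assumed. It is the chance of at least one false positive when every null is true, not the share of significant results that are false.
- *Pearson invalidates the MMT result.* With 11 ordered grades and no rank alternative stated for correlations, Pearson is a suboptimal choice, not a fatal one.

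Adding MEP also brings a difficulty. The article foresees patients with no evoked MEP, who have no latency or conduction time. MEPs are recorded from a hand and a leg muscle with stimulation on both sides, so the set of tests stays undefined until muscle and side are fixed.

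**Conclusion.** The concern holds as an internal contradiction. The Introduction and Discussion promise a correlation that includes electrophysiology; the analysis as fixed contains none, so the conduction part of the coupling claim has no linking analysis. This rests on the text alone and needs no assumption. It should be corrected before analysis, because it bears on the study's headline conclusion and the measures are already planned at both visits.

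The remaining points carry less weight. The multiplicity range of 9.8% to 64% depends on assumed region counts and independence. The arm term matters only under pooling of post-treatment or change values. The choice of Pearson for MMT is a matter of improvement.

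**What to change.** Rewrite the correlation section as follows, and align the Abstract, Study setting and Discussion with it.

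- Add amplitude, latency and central motor conduction time. Correlate them with ReHo in prespecified M1 and thalamus regions, and with Fugl-Meyer and MMT. Keep ReHo with the two clinical scores.
- Fix the muscle and side in advance, and state whether baseline, post-treatment or change values are used.
- Use rank-based partial correlation. It suits MMT and allows patients without an evoked MEP to take the worst rank instead of being dropped, which would select on severity. If change values are used, the rule must also say how a response absent at one or both visits is ranked.
- If post-treatment or change values are pooled over the arms, add arm to gender, age and course.
- Control the false discovery rate over the fixed set, or label it exploratory. With one M1 and one thalamus region and one muscle and side, the set is 2 × 3 + 3 × 2 + 2 × 2 = 16 tests. Unadjusted, 1 − 0.95^16 = 56% if independent.

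If the MEP correlations are not wanted, limit the conclusion to clinical-imaging association.

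The cost is a change of wording, a little more analysis and fewer nominally significant correlations. No new data are needed.

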## Methods

### Study setting

This is a prospective functional neuroimaging and neurotic electrophysiological study with a case-control design between the PSD with the HC groups and a randomized controlled design within the 3 PSD groups (OAKT group, ocular acupuncture group, and kinesitherapy group). Using fMRI scanning and the TMS-MEP technique, we will assess the central-peripheral neuronal function changes of PSD as well as the coupling effects of OAKT on them. This trial was authorized by the Institutional Review Board of Chengdu University of Traditional Chinese Medicine in April 2022 (reference number: 2022KL-027) and registered (ChiCTR2200060483) at the Chinese Clinical Trial Registry in June 2022. We plan to enroll 90 participants at the Hospital of Chengdu University of Traditional Chinese Medicine from Aug 31, 2022, to Dec 31, 2023. All eligible subjects will be evaluated by fMRI scanning, TMS-MEP examination, and the MMT and Fugl-Mayer assessment following enrollment and on the last day after 4-weeks of waiting (for HC subjects) or intervention (ocular acupuncture, kinesitherapy, or OAKT for PSD subjects, respectively). MMT and Fugl-Meyer score, ReHo value, cluster size, active or positive brain regions and their MNI coordinates, amplitude (AMP), potential latency (PL), and central motor conduction time (CMCT) in the cortical region will be measured, and Pearson correlation analysis will be performed to assess the relationship between clinical and imaging outcomes. This trial will be conducted in accordance with the Standard Protocol Items: Recommendations for Interventional Trials (SPIRIT) (43). Figure 1 displays a flow diagram.

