### Interventions

PSD participants will be randomized to the ocular acupuncture (OA) group, the kinesitherapy (KT) group, or the OAKT group after enrollment.

Subjects in the OAKT group will undergo kinesitherapy after receiving ocular acupuncture stimulation at the “Upper-Jiao Area” (ACU 1), “Lower-Jiao Area” (ACU 2), “Liver Area” (ACU 3), and “Kidney Area” (ACU 4) (16) (Figure 2). This involves a series of advised exercise training consisting of warm-up exercises (low levels of aerobic exercise), exercise training (including aerobic training, walking training, treadmill training, resistance training, upper limb flexion adduction-abduction exercise, lower extremity knee flexion-extension exercise, flexibility training), and relaxation training (stretching exercise) (46). Needles for ocular acupuncture will remain embedded until the day's exercise training is finished. OAKT will be manipulated once a day, 5 days a week, for 4 weeks, with 2 days off between courses. Sweating, breathing, pulse, and blood pressure measures will be used to adjust the exercise prescription.

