### Sample size

This is a central-peripheral coupling mechanism study rather than a clinical trial. As human-based neuroimaging mechanism studies differ from clinical trials, sample size cannot be estimated using clinical trial computational methods. According to the sample size calculation of imaging studies at home and abroad (47), the sample size is usually 6–12 cases in each group. We determined the sample size as 15 cases per group in accordance with the minimum statistical requirements, considering the drop-out that could be brought on by subjects' compliance and removing the scenario that patients' excessive head movement might influence the data in the statistical analysis progress during fMRI scanning. To keep the statistical results accurate and reliable, 45 healthy controls must be matched simultaneously. In total, 90 subjects-−15 in the OAKT group, 15 in the OA group, 15 in the KT group, and 45 in the HC group—are required for this study.

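### The ReHo–motor correlation across PSD patients has no treatment-arm term, so with post-treatment or change values arm effects can create or mask it, and at no time point is it specific to OAKT

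*Protocol article*

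**What the plan says.** Under Correlation analysis between clinical and imaging data, the protocol article plans a "correlation analysis between ReHo values and clinical indexes of PSD" and specifies it as a Pearson analysis of the two motor scores against ReHo: "Gender, age, and course will be included as covariates", tested at 0.05. Course most naturally means course of disease; nothing suggests that it stands for treatment.

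The PSD patients are not a single treated group. Study setting describes "a randomized controlled design within the 3 PSD groups (OAKT group, ocular acupuncture group, and kinesitherapy group", Interventions says "PSD participants will be randomized to the ocular acupuncture (OA) group" or one of the two other arms, and Sample size gives "15 in the OAKT group, 15 in the OA group, 15 in the KT group, and 45 in the HC group". OA uses the same acupoints as OAKT without exercise; KT uses the same exercise without needling.

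The Discussion repeats the Pearson analysis for PSD, says that it investigates the association of the outcomes, and continues "to finally exploit the central-peripheral linkage control mechanism and coupling effect of OAKT on PSD".

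Clinical scores are taken at baseline and at study completion. The correlation section does not say whether baseline, post-treatment or change values are used.

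**The concern.** Randomised arm is the one factor the trial itself manipulates, and it is absent from a covariate list that is otherwise spelled out. After treatment, arm can be a common cause of ReHo and of motor score. A coefficient over all PSD patients then mixes two things: differences between arm means, and the association between patients within an arm.

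The error can go either way. If OAKT raises both measures independently, the combined patients correlate even though, within any arm, patients with larger ReHo changes gain no more than the others. If needling mainly moves ReHo (OAKT and OA) and exercise mainly moves the score (OAKT and KT), the arm means pull the coefficient down and a real within-arm association may be missed.

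Specificity is a separate matter. One coefficient over three arms cannot tell OAKT from OA or KT, yet the Discussion carries the analysis towards a statement about OAKT. That is the study's central mechanistic claim.

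**Working it through.** **Figures in the plan.** The protocol states no expected correlation, power or sample size for this analysis, so there is nothing of that kind to reproduce. The total adds up: 3 × 15 + 45 = 90. At most 45 PSD patients enter, because only subjects with complete data are analysed. Patients not receiving OAKT: 15 + 15 = 30 of 45.

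**Inputs.** From the protocol: three arms of 15, three covariates, alpha 0.05 (two-sidedness is stated for the clinical analyses and assumed here). Assumed: arm shifts *d* in within-arm SD units, and a within-arm correlation ρ of 0 or 0.4.

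**Closed form.** With equal arms and unit within-arm SD, the combined correlation is

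r = (ρ + C) / √[(1 + Vx)(1 + Vy)],

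where C is the covariance of the arm means and Vx, Vy are their variances.

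*Create case* (ρ = 0, OAKT alone shifted by *d* on both variables): C = Vx = Vy = (2/9)d².
- d = 0.5: 0.056/1.056 = 0.05
- d = 0.8: 0.142/1.142 = 0.12
- d = 1.0: 0.222/1.222 = 0.18
- d = 1.5: 0.500/1.500 = 0.33

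*Mask case* (ρ = 0.4, needling shifts ReHo in OAKT and OA, exercise shifts the score in OAKT and KT): Vx = Vy = (2/9)d² and C = (1/3 − 4/9)d² = −(1/9)d².
- d = 0.5: (0.4 − 0.028)/1.056 = 0.35
- d = 0.8: (0.4 − 0.071)/1.142 = 0.29
- d = 1.2: (0.4 − 0.160)/1.320 = 0.18

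**Rejection rates by simulation** (10,000 to 20,000 trials of 3 × 15, two-sided 0.05). Ranges cover runs with and without three covariates unrelated to outcome.

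| Arm shift | Create: no arm term | Create: arm included | Mask: no arm term | Mask: arm included |
|---|---|---|---|---|
| 0.3 SD | 5% | 5% | 72–75% | 74–77% |
| 0.5 SD | 6–7% | 5% | 64–67% | 74–77% |
| 0.8 SD | 12–13% | 5% | 46–48% | 74–77% |
| 1.0 SD | 21–23% | 5% | 32–34% | 74–77% |
| 1.5 SD | 61–65% | 5% | 7% | 74–77% |

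The higher power figure in each range is the run without covariates. With no arm effect and the three covariates in the model, the two analyses nearly agree: 4.8% false positives for both, and power 76.5% without arm against 74.6% with it.

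**Cost of the arm term.** Residual degrees of freedom are 45 − 2 − 3 = 40 as planned and 45 − 2 − 5 = 38 with two arm indicators. The r detectable with 80% power is tanh[(1.960 + 0.842)/√(45 − k − 3)]: 0.42 for k = 3 covariates and 0.43 for k = 5.

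**What can be said about OAKT alone.** In the OAKT arm (n = 15, three covariates, 10 degrees of freedom) significance needs |r| of about 0.58, and 80% power needs a true r of about 0.73. For the difference in slopes between OAKT and OA, without covariates, power is about 17% if the OAKT correlation is 0.4 and the others are 0, and about 35% if it is 0.6.

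**The case against.** The document never says that the arms are pooled; it refers to ReHo values of PSD, and a condensed article may leave the grouping to a fuller plan. This tempers the wording but does not remove the point. The covariates are listed without arm, the analysis is described for PSD, and no section supports a split by arm.

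A stronger objection concerns the time point. A reader might infer that the planned correlation is biased whatever is correlated. The documents do not support that. With baseline values, arm cannot confound beyond chance, and a correlation across all PSD patients would suit the case-control aim. The create-or-mask mechanism therefore holds only for post-treatment or change values.

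The size is also uncertain. No arm effects are given, and at 0.3 to 0.5 SD the false-positive rate barely moves. The create case further assumes that OA and KT shift neither variable, although each shares a component with OAKT.

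A reader might also take the Discussion to equate this coefficient with the OAKT coupling effect. It does not quite say so: it speaks first of association, and the coupling effect follows as an aim.

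Finally, parallel shifts in arm means may be part of the mechanism, so adjustment could remove signal. But those shifts belong in the comparison of arms, and the unadjusted coefficient cannot separate them from an association between patients.

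**Conclusion.** The point stands in conditional form. Read as written, the analysis combines three randomised arms with no arm term. If post-treatment or change values are used, the coefficient can err in either direction. The distortion is small at 0.5 SD in the create case, already noticeable there in the mask case (a loss of about 10 percentage points of power), and serious in both from about 1.0 SD. These sizes rest on assumed arm effects and an assumed within-arm correlation of 0 or 0.4, not on figures in the protocol.

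The lack of specificity needs no such assumption. With post-treatment or change values two thirds of the patients have not had OAKT, and at baseline nobody has been treated. A single coefficient across PSD patients therefore cannot support an OAKT-specific conclusion.

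Even with arm included, the coefficient describes association between patients within arms. It is not a within-patient association, because each patient contributes one pair of values.

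**What to change.** - In the correlation section, state that change values (or post-treatment values) are correlated, and add treatment arm as two indicator terms beside gender, age and course. This costs 2 of 40 degrees of freedom and needs no new data or patients.
- In the Discussion, describe the result as a within-arm, between-patient association across PSD patients, not as a coupling effect specific to OAKT.
- If arm-specific slopes or an arm-by-ReHo interaction are reported, give them with 95% confidence intervals and label them exploratory. The interaction takes two further degrees of freedom (38 to 36) and has low power at 15 per arm, so it should not carry the conclusion about OAKT.

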Regional homogeneity (ReHo), a typical fMRI analysis, can indirectly reflect the time synchronization of spontaneous neural function activities in a specific brain region. The Kendall's Coefficient Concordance (KCC) will be used to quantify the local consistency of time series between each voxel in the entire brain and the nearest 26 voxels around it by using REST software in Matlab. Each individual receives a ReHo image by computing the KCC value of each voxel. After normalization, the average ReHo image of each subject will be derived by dividing the KCC value of each voxel by the average KCC value of the entire brain. The estimated ReHo value corresponds to the KCC value, which runs from 0 to 1. The closer it is to 1, the more consistent this voxel's activity is in time series with its neighboring voxels, reflecting brain local neuronal activity synchronization. The calculation is expressed as follows:

$$\begin{array}{l} \text{ReHo}=\frac{\sum {\left({\text{R}}_{\text{i}}\right)}^{2}-\text{n}{\left(\text{R}\right)}^{2}}{{\text{k}}^{2}\left({\text{n}}^{3}-\text{n}\right)/12} \end{array}$$

The SPM12 in Matlab will be used to analyze the obtained ReHo value. MNI coordinates of the associated regions, the size of the clusters, and the active or positive brain regions will all be noted before and after the intervention.

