#### Clinical and electrophysiological data analysis

SPSS 23.0 will be used for data analysis. For measurement data, the *T*-test or ANOVA with 95% confidence intervals will be used to compare groups if the distribution is normal, else a Non-parametric Test will be performed. For enumeration data, a chi-square test will be used. A two-sided threshold of *P* < 0.05 will be considered statistically significant.

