#### Neuroimaging data analysis

SPM12 software will be used to perform paired *t*-tests on the acquired ReHo value. The statistical threshold voxel-level will be *P* < 0.001 with multiple comparisons corrected by FEW (family-wise error), cluster level α < 0.05. More than 10 continuous voxels will be significant.

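### ReHo-clinical correlations are called significant at P<0.05 each, with two scores, an unfixed number of ReHo values and no multiplicity correction

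*Protocol article*

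**What the plan says.** The section Correlation analysis between clinical and imaging data plans "a Pearson correlation study between the MMT score, Fugl-Meyer score, and ReHo values of PSD", with adjustment: "Gender, age, and course will be included as covariates". Its decision rule is: "The statistical threshold of *P* < 0.05 will be considered statistically significant". The section gives no correction for the number of correlations and does not call the result exploratory. It also leaves open how many ReHo values enter, which time point is used and whether the three patient arms are pooled.

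The section just before it, Neuroimaging data analysis, does deal with multiplicity: "multiple comparisons corrected by FEW (family-wise error), cluster level α < 0.05". That control is attached to the paired t-tests on ReHo and is not carried over to the correlations.

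Under Functional neuroimaging outcomes, ReHo quantifies the "local consistency of time series between each voxel in the entire brain and the nearest 26 voxels around it". The regions recorded are those that emerge from the map analysis. The Discussion names the primary motor cortex (M1) and the thalamus as the brain targets, and lists the correlation of the two scores with ReHo among the analyses that lead to the coupling conclusion.

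**The concern.** Two consecutive sections treat multiplicity differently. The pre-post maps have family-wise control. The correlations, which relate brain measures to motor scores, are each tested at 5%. Every ReHo value that enters brings two tests, so the error rate for the set exceeds 5% even with one region and rises with each region added.

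What is at stake is how a significant correlation is read. The article intends to use such results in explaining how the treatment links central and peripheral function. If one of several uncorrected correlations crosses 0.05, the stated rule gives no way to separate it from a chance result, and nothing tells the reader to treat it as exploratory.

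**Working it through.** **Inputs**
- Per-test threshold: 0.05 (Correlation analysis section). Sidedness is not stated there. Two-sided is assumed from Clinical and electrophysiological data analysis: "A two-sided threshold of *P* < 0.05 will be considered statistically significant".
- Scores: 2 (MMT and Fugl-Meyer).
- Covariates: 3 (gender, age, course).
- Patients: 3 × 15 = 45 (Sample size), if arms are pooled and nobody is lost. Only subjects with complete data are analysed, so 45 is the maximum.
- Number of regions R: not given, so it is varied as an assumption.

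The article states no family-wise error rate for the correlations, so there is no figure to reproduce. A single test gives 0.05.

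**Step 1. Independent tests.** With k = 2R tests, the chance of at least one false positive is 1 − 0.95^k.

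| Regions R | Tests k | Chance of at least one false positive | Expected false positives (0.05 × k) |
|---|---|---|---|
| 1 | 2 | 9.8% | 0.1 |
| 2 | 4 | 18.5% | 0.2 |
| 4 | 8 | 33.7% | 0.4 |
| 7 | 14 | 51.2% | 0.7 |
| 10 | 20 | 64.2% | 1.0 |
| 20 | 40 | 87.1% | 2.0 |

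Two regions stand for M1 and thalamus, and four for both structures on both sides.

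**Step 2. Correlated tests.** Both scores measure motor ability, and neighbouring regions share signal, so independence overstates the risk. Partial correlations were simulated under the null (n = 45, 3 covariates, 8,000 datasets per setting), assuming a correlation of 0.7-0.8 between scores and 0-0.5 between regions:
- 2 regions: 13-16%
- 4 regions: 24-30%
- 7 regions: 33-46%
- 10 regions: 42-58%
- 20 regions: 58-83%

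**Step 3. Repetition.** The article does not say whether baseline, end or change values are used, or whether arms are analysed separately. Four regions with two scores at two time points make 16 tests: 1 − 0.95^16 = 56%. The same in three arms makes 24 tests: 1 − 0.95^24 = 71%. Both figures assume independence, which is doubtful for repeated time points in the same patients.

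**Step 4. Does the correction of the maps help?** If ReHo values were taken only from clusters that survive the corrected pre-post analysis, the correction would limit false pre-post changes. It would not limit false associations between those clusters and the scores. Each surviving cluster would still bring two tests at 0.05.

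**Step 5. Effect of family-wise control.** The critical |partial r| is t/√(t² + df), with df = 45 − 2 − 3 = 40.
- At 0.05 it is 0.304.
- For 8 tests under Bonferroni (0.05/8 = 0.00625) it is 0.415, and the error for the set is 1 − (1 − 0.00625)^8 = 4.9%.
- For 20 tests (0.0025) it is 0.454.

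With 8 tests, a correlation between 0.304 and 0.415 is significant under the article's rule but does not reach the Bonferroni threshold.

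**The case against.** The strongest defence has four parts.

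**The set of regions is probably small.** A reader might infer from the whole-brain computation of ReHo that the number of correlations is unlimited. The article does not support that. Computing ReHo in every voxel does not mean correlating every voxel. The Introduction and Discussion name a specific pathway with two brain structures, and the values may come from clusters that survive correction. This stands: the number is unspecified, not unlimited. The defence does not remove the problem, because one region with two scores already exceeds 5%.

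**Which regions are used may be set elsewhere.** A condensed article can leave that to a fuller protocol or analysis plan, so the missing list is not itself a fault. This also stands. The threshold, however, is stated here, and a later list of regions would not correct it.

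**A voxelwise reading is not in the text.** A reader might picture uncorrected correlation maps with large numbers of false voxels. The correlation section gives no voxel or cluster threshold and describes no mapping, so no such figures are counted here.

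**The correlations are not the only evidence, and this is a mechanism study.** The Discussion bases its conclusions on fMRI, TMS-MEP and clinical scales, and presents the Pearson analysis as an addition. The Sample size section says the study is not a clinical trial. Both are fair and lower the weight of the point. They do not justify the rule, because the section declares significance without labelling the correlations exploratory.

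**Conclusion.** The point holds in a limited form. The stated rule gives a family-wise error above 5% for any number of regions, because two scores are tested at 0.05 each. For M1 and thalamus, on one or both sides, the chance of at least one false-positive correlation is about 13-34%, depending on the assumed correlations. It reaches one half at 7 regions if tests are independent, and needs roughly 10 to 20 if they are correlated.

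A reader might conclude that a chance finding is likely, or is to be expected. The documents do not support that, because they give no region count. For the named targets the risk is below one half, with 0.2 to 0.4 false positives expected among 4 to 8 tests. The region counts, the correlations between scores and regions, two-sided testing and full retention of 45 patients are assumptions.

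The rule should be corrected. The treatment comparisons and the pre-post maps do not depend on it.

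**What to change.** Replace the threshold sentence in the correlation section before the data are seen:
- Name a short list of region-score pairs from the pathway the article already targets, for example ReHo in M1 and thalamus with MMT and Fugl-Meyer. State the time point and whether arms are pooled.
- Test these pairs with Holm at two-sided family-wise 0.05. With four pairs, the smallest P value is compared with 0.05/4 = 0.0125.
- Report all other correlations as exploratory estimates with 95% confidence intervals and no significance claim.
- If correlations are mapped voxelwise, apply the cluster-level family-wise threshold given in Neuroimaging data analysis.

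This takes a few sentences and needs no new data or patients. The cost is that fewer correlations will be called significant. At n = 45 with three covariates and 8 tests, a correlation must reach about 0.415 rather than 0.304 under Bonferroni. Holm's first step uses the same limit and its later steps are less strict. The shorter the list, the smaller this loss.
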